#### Secondary outcome: evaluation of implementation

The professionals’ attitudes toward working with the CPG will be evaluated using descriptive statistics. Additionally, McNemar tests will be used to compare the attitude at the start of the trial with that at the end of the trial. Since the study was not powered for this outcome measure, the results are only explorative. The professionals’ compliance with working with the CPG will also be evaluated using descriptive statistics. For the intervention group, we will additionally evaluate the influence of the professionals’ compliance on the incidence of WSLs. Chi-square tests will be used to compare the patients’ experiences with the preventive strategies used (CPG versus usual strategies).

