### Randomization

Utilization of both the CPG and the usual preventive measures within the same practice would inevitably result in some control patients receiving some CPG-recommended care, which would dilute the effect of the intervention. To prevent such contamination of interventions between study groups, we will perform cluster randomization at the level of practices rather than individuals. Using a software program, practices will be assigned to either the *intervention arm* or the *control arm* by an independent statistician who is not familiar with the practices.

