#### Sample size and power calculation

We have calculated the number of patients needed to detect a difference in the proportions of patients with newly developed or enlarged WSLs between the intervention group using the CPG and the control group using standard preventive strategies. Earlier studies show that more than 1 in 4 orthodontic patients develop at least one new WSL during the course of orthodontic treatment [3]. Assuming a power of 80 %, a significance level of 5 %, and an ICC of 0.05 to correct for clustering, we calculated that we must include a minimum of 14 orthodontic practices with 50 patients per practice to detect a medium effect size of 0.4 for reduction in newly developed WSLs. The effect size was arbitrarily chosen, as no previous data establish what would constitute a clinically relevant change. The study is powered to detect an effect of 15 % absolute reduction in prevalence of WLS, under the assumptions specified above. Assuming a drop-out rate of 20 %, we plan to recruit a total of 60 patients per participating practice, resulting in a total inclusion of 840 patients. In a regular orthodontic practice, about 40 patients receive full fixed appliances each month. To account for an overestimation of the number of patients to potentially be included in the practices, we will have a 2-month inclusion period.

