#### Primary outcome

To account for the data clustering (in orthodontic practices), a multilevel logistic regression analysis will be applied on patient data, using the presence of new WSLs at T2 (yes/no) as the outcome, and the type of intervention (CPG or usual preventive measures) as the predictor. In this model, the regression coefficient of the predictor “intervention versus control” indicates the effectiveness of the intervention. Given the expected distribution of outcomes, we anticipate the use of binomial logistic regression with a logit link function. We will also examine the influences of age at start of treatment, gender, patients’ opinion on preventive measures, patients’ initial oral health status, patients’ initial oral hygiene status, and patients’ initial sugar intake on the primary outcome measure, by including these factors one by one as predictors in the regression model. These covariates are known to potentially influence the development of WSLs during orthodontic treatment [3, 9]. We do not anticipate a high number of missing values. However, in the event that we do have high numbers of missing values, we will apply a multiple imputation method prior to the planned analyses.

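### Patients' experiences are compared between arms with chi-square tests that ignore the randomisation by practice, so the uncertainty of this secondary comparison is understated

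*Protocol article*

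**What the plan says.** The Randomization section of the protocol article states that "we will perform cluster randomization at the level of practices rather than individuals". The Data collection section on patients' experience sends the questionnaire to every included patient, and the Sample size section plans 60 of these per practice in 14 practices.

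For the between-arm comparison of the answers, the section on the secondary outcome (evaluation of implementation) says: "Chi-square tests will be used to compare the patients’ experiences with the preventive strategies used (CPG versus usual strategies"). It mentions no adjustment for practice, and neither does any other section for this comparison.

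Elsewhere the protocol does allow for clustering. The sample size is derived "Assuming a power of 80 %, a significance level of 5 %, and an ICC of 0.05 to correct for clustering". The primary analysis section says: "To account for the data clustering (in orthodontic practices), a multilevel logistic regression analysis will be applied on patient data".

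**The concern.** Patients of one practice share its staff, its routines and, in the control arm, its own usual preventive measures. Their answers about the care they received cannot be assumed independent. A chi-square test on pooled patients takes the number of patients as its information, although the arms differ by which practices were allocated to them. Its reference distribution is then too narrow whenever answers correlate within practices.

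Patients' views are one of the three listed process outcomes, and this is the only between-arm test named for them. A difference that merely reflects which practices fell into which arm could be read as an effect of the guideline on patient experience.

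This is not a detail that a condensed article leaves to a fuller document. The article names the test, and the named test does not fit the design.

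**Working it through.** **Inputs from the protocol.** 14 practices; 50 evaluable and 60 recruited patients per practice; 5 % significance level; 80 % power; ICC 0.05, set for the lesion outcome.

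**Inputs that are assumptions.** A two-sided test and seven practices per arm (neither is stated). Responders per practice, taken as 30 to 60, because no response rate is given. The questionnaire ICC, varied over 0.01, 0.02 and 0.05.

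**Step 1: the plan's own figure.** The design effect is DE = 1 + (m − 1) × ICC, where m is the number of patients per practice. With m = 50 and ICC 0.05, DE = 1 + 49 × 0.05 = 3.45.
- Standardised effect 0.4: 99 per arm without clustering; 99 × 3.45 = 341.6; 341.6 / 50 = 6.83, rounded up to 7 practices per arm.
- 25 % v 10 % (the stated 15-point reduction): 100 per arm; 100 × 3.45 = 345; 345 / 50 = 6.9, rounded up to 7 per arm.

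Both give the stated 14 practices. The same design effect is therefore the natural yardstick for the questionnaire.

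**Step 2: true type I error of the unadjusted test.** For a two-category item (1 degree of freedom), the true error is 2 × [1 − Φ(1.96 / √DE)].

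| Responders per practice | ICC 0.05: DE | ICC 0.05: error | ICC 0.02: DE | ICC 0.02: error | ICC 0.01: DE | ICC 0.01: error |
|---|---|---|---|---|---|---|
| 30 | 2.45 | 21.1 % | 1.58 | 11.9 % | 1.29 | 8.4 % |
| 40 | 2.95 | 25.4 % | 1.78 | 14.2 % | 1.39 | 9.6 % |
| 50 | 3.45 | 29.1 % | 1.98 | 16.4 % | 1.49 | 10.8 % |
| 60 | 3.95 | 32.4 % | 2.18 | 18.4 % | 1.59 | 12.0 % |

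At ICC 0.05 the standard error is too small by a factor of √2.45 = 1.57 to √3.95 = 1.99. With only 20 responders per practice the error is still 16 % (DE 1.95).

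**Step 3: check by simulation.** Beta-binomial data were generated with seven practices per arm, ICC 0.05, true proportions of 0.25, 0.5 and 0.8, and 40,000 replicates. The unadjusted test rejected in 20.5 to 21.3 % (m = 30), 29.2 to 29.5 % (m = 50) and 32.2 to 32.7 % (m = 60). A continuity correction lowers this only to about 18 to 19 %, 27 to 28 % and 30 to 31 %.

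**Step 4: does a practice-level analysis repair it?** A t-test on the practice proportions, seven against seven, rejected in 4.9 to 5.1 % of the simulated data (m = 30 and 50).

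**Step 5: items with more categories.** The protocol does not give the answer format of the patient questionnaire. If an item had five levels, a 4-degree-of-freedom chi-square test at ICC 0.05 rejected in 42 % (m = 30) and 61 % (m = 50) of simulations. The two-category figures are therefore not a worst case.

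**The case against.** - **The ICC is borrowed.** The value of 0.05 was set for a photographic lesion outcome, and nothing in the protocol gives an ICC for questionnaire answers. This stands. A reader might infer that the protocol's own assumptions imply a false-positive rate above 20 %, but they do not: the rate is conditional on 0.05 carrying over. It is also tempting to say that experience of care must cluster at least as strongly as lesions. That is plausible, because one questionnaire aspect asks what the practice delivered, but the documents do not establish it.
- **The number of responders is assumed.** This also stands. The 50 per practice in the sample size section is what remains after drop-out, not a questionnaire return.
- **The comparison is not confirmatory.** The design is a hybrid type 1 study whose implementation results are described as preliminary. This stands and limits the severity. The remark that results are explorative follows the McNemar comparison of professionals' attitudes and refers to that outcome. Even if it were extended to the patient questionnaire, it would excuse low power, not a test with the wrong error rate.
- **The null may not be true.** The guideline is meant to change whether patients receive the recommended measures, so a strict null is less plausible for those items. For them the harm is an overstated precision rather than a false positive. The correction is the same.
- **Only some practices may be involved.** The Implementation program section speaks of evaluating the process in a limited number of practices, whereas the questionnaire goes to all included patients. Fewer practices would not reduce the design effect, which depends on patients per practice.

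**Conclusion.** The planned test is wrong as written for a practice-randomised comparison. At any positive ICC it understates the uncertainty.

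How far it does so is conditional. It is about 21 to 32 % instead of 5 % if the questionnaire ICC is 0.05 and 30 to 60 patients per practice respond. With 30 to 50 responders it is about 12 to 16 % at an ICC of 0.02 and about 8 to 11 % at 0.01. All of these figures assume a two-sided test of a two-category item and, in the simulations, seven practices per arm.

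A reader might go further and conclude that spurious effects will be reported, or that the trial's main result is compromised. Neither follows. Even at 32 %, most null comparisons would stay non-significant, so practice differences could, not would, appear as effects of the guideline. The primary lesion outcome has its own multilevel model and is unaffected. This should be fixed, but it does not put the trial's main conclusion at risk.

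**What to change.** In the section on the secondary outcome, replace the chi-square tests with one of the following:
- a multilevel logistic model (ordinal for items with ordered categories) with practice as random intercept and a small-sample correction, which matches the approach already chosen for the primary outcome; or
- a t-test on practice-level proportions, using the practices that contribute questionnaires. With all 14 this has 14 − 2 = 12 degrees of freedom.

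Report each between-arm difference with a cluster-adjusted 95 % interval. State which practices contribute, so that the analysis agrees with both the Implementation program and the Data collection sections.

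The cost is a change of analysis wording, slightly more analysis work and wider intervals. No additional patients, practices or data are needed.

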## Discussion

This study will investigate the effectiveness of a newly developed guideline to improve oral health during orthodontic treatment, while simultaneously illuminating potential difficulties in adopting a guideline in general orthodontic practice. The innovative features of this study include the risk-based CDSS that discriminates between patients’ oral health statuses with regard to preventive measure utilization in general orthodontic practices. Most studies focusing on WSL prevention apply the preventive intervention to each patient in an experimental setting, resulting in overtreatment and a disconnect from the real-world conditions in which the intervention is to be applied [16, 17]. Additionally, one of the overreaching goals of this initiative is to create a gold standard for WSL prevention during orthodontic treatment, against which future studies can compare new promising preventive measures and the readiness of clinicians to change and adopt new treatments. By doing so, we want to help bridge the gap between science and orthodontic clinical practice and improve the quality of oral health care [18, 19].

### Trial status

Six practices have been recruited. Baseline data regarding WSL incidence and preventive strategies have been analyzed. At the present phase of the trial, we are actively recruiting the remaining eight practices.

### Consent

Written informed consent was obtained from the patient for the publication of this manuscript and the accompanying images. A copy of the written consent is available for review by the Editor-in-Chief of this journal.

## Abbreviations

CDSS: computerized clinical decision support system
CPG: clinical practice guideline
EPF: electronic patient file
WSL: white spot lesion
